#### JJI Staff

We devised questionnaires for JJI staff (group workers, team leaders, psychologists) about working with families and about using the family perspective in their thinking and in day-to-day interventions. The questionnaire has two parts, part A and part B. Part A contains 12 items to be rated on a five-point scale and includes questions such as “Do you invite parents of every mentor-child for a meeting?”, “Do you invite parents of every mentor-child for a tour through the facility?”, “Do you inform parents on the same day when their child was involved in an incident?”, and “If parents are divorced, do you involve both parents in the same way?”. Part B contains 17 items to be rated on a scale of 1-10. This part includes questions such as “How satisfied are you with the course of the contact with the parents?”, “How satisfied are you with the way in which you involve parents during their son’s stay?”, and it includes statements such as “Parents are difficult to work with”, “Parents are indispensable for reducing recidivism”, and “Parents are a source of support for staff”.

These questionnaires will be filled out every three months. On an additional form, psychologists will note where the adolescent is going to live after leaving the short-term stay group.

To assess if staff members adhere to the guidelines of the FC program, they will use logbooks and will fill out short forms on family-centered activities undertaken. This will enable us to assess program integrity. The overviews of these logs are shared during team meetings and with the managements, enabling managers and team leaders to monitor and direct the organization of family-centered activities.

### Procedure and Instruments of the Qualitative Part of the Study

Before the interview, the participant will complete a short demographic questionnaire. The interview will be about 60 to 90 minutes and will be audio recorded. The recording will be stopped during the interview if so requested by the participant. The semi-structured interviews will be conducted by qualified trained students enrolled in the last year of either a Bachelor’s or a Master’s program of Social Work or another social science.

The interviews are structured using a topic list [43]. We drafted a topic list for each group of participants (adolescents, parents, FC group workers, and UC group workers). The topic lists were devised following deductive and inductive strategies. Deductively, topics were derived from a review of literature of factors that contribute to the success of family-centered work in institutions similar to JJIs. Inductively, experiences from group workers, parents, and adolescents were used to supplement the topic list. Additionally, each interview can influence the construction of the topic list as new themes may arise. The themes of the final topic lists are represented by questions and are displayed in Table 1 and Table 2. Although the topics follow a logical order in themes, the topic lists will be used in the order as the interviewer sees appropriate, based on the answers of the respondents. Based on further subtopics and keywords the interviewer will probe for more information on each main theme as specified in Tables 1 and 2.

**Table 1 table1:** Main themes of the topic lists for interviewing adolescents and parents.

Adolescents and parents	Adolescents only	Parents only
To what extent are parents currently involved?	Do you consider the involvement of your parents as being important?	To what extent and in which way do you wish to be involved?
How can parents be motivated for involvement?	How should the JJI involve parents?	
What are your expectations of staff in involvement and contact?	How can the JJI motivate adolescents for FC?	
Which factors influence involvement and in which ways?	Which reasons do adolescents have to object to FC?	
How can we explain the surprising preliminary finding in the quantitative pilot stage that parents and youths report few family problems while they also report to be motivated for family therapy?		

**Table 2 table2:** Main themes of the topic lists for interviewing group workers.

Group workers FC and UC	Group workers FC only	Group workers UC only
How do you feel about the involvement of parents?	What is Family-centered Care?	What is parental participation?
What do you think about the following elements in parental participation: knowing, discussing, activities, and deciding?	Which changes in practice did you notice since the implementation of FC?	What do you expect of FC when it will be implemented in your group in the future?
How is the atmosphere in your team?	How has FC been implemented in your team?	Which changes are necessary before your team is ready for the implementation of FC?
What is your role within your team?	How do you feel about the FC training?	
Do you have sufficient skills for involving parents?		
Do your colleagues have sufficient skills for involving parents?		
To what extent do managers support you in involving parents?		
What pros and cons of FC do you see?		
Do you have tips for involving parents?		

### Analyses

#### Quantitative Analyses

All statistical analyses will be performed using SPSS 23. In a future paper, we will provide a flowchart of participants in our study, including reasons for exclusion. Descriptive statistics will be presented as means and standard deviations for all continuous variables and subscales. Additionally, frequency distributions or qualitative descriptions of all categorical variables will be presented for each group. The groups will be defined as FC or UC. We will test if these groups differ on demographic factors. If these differences exist, we will use these factors as covariates in our analyses. If necessary, we will also include the JJI in which an adolescent is placed as a covariate. We will perform within-group pre-post comparisons, between-group comparisons (FC vs UC), and repeated measures analyses. The selection of a specific test will depend on which hypothesis is tested and on the characteristics of the corresponding data (eg, categorical, ordinal, or interval level and normally or non-normally distributed). Table 3 shows the planned analyses to test our hypotheses for comparing FC with UC in case of normally distributed data. For combining the within-group pre-post comparisons and the between-group comparisons in our analyses, we will use the repeated measures ANOVA. Because the normality of the distribution of the data cannot be determined beforehand, the final analyses will be selected after the data is gathered. In analyzing the hypotheses, two-tailed analyses will be performed and we will correct for multiple testing.

**Table 3 table3:** Planned analysis for between-group hypotheses.

Hypothesis	Data source	Analysis
FC increases parents’ involvement with their detained child	Registration logs visits	Unpaired *t* test
FC increases the motivation of the adolescents and parents for accepting treatment and guidance by JJI staff and for taking part in family meetings	ATMQ youth total score Motivation items youth	Unpaired *t* test Pearson’s Chi-square test
	Motivation items parents	Pearson’s Chi-square test
FC adolescents show less problem behavior	Incidents in JJI Cannabis database	Unpaired *t* test Unpaired *t* test
FC improves family interactions	FES	Unpaired *t* test
FC parents experience less parenting stress	PSQ	Pearson’s Chi-square test
FC youth more often return to their families’ home upon discharge	Registrations logs living situation after discharge	Pearson’s Chi-square test
FC enhances adolescents’ and parents’ satisfaction with the JJI	Satisfaction questionnaire-A Satisfaction questionnaire-B	Pearson’s Chi-square test Unpaired *t* test
In FC groups, JJI staff members are more satisfied, feel more confident in their contact with parents, and more often incorporate the family perspective in thinking	Questionnaire staff-A	Generalized estimating equations
	Questionnaire staff-B	General linear model repeated measures

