**Figure 1 figure1:**
[figure not shown]
Study design.

In our study, we employ a mixed methods design in which quantitative and qualitative research methods are combined [27]. In mixed methods studies, qualitative and quantitative stages of data collection can occur concurrently or sequentially and can be nested in each other [28,29]. We utilize an explanatory sequential mixed methods design [30] with a large concurrent stage. The first stage of the sequence consists of the quantitative pilot. The second stage of the sequence involves concurrent qualitative and quantitative components. In the third stage, which is integral part of the study, we distinguish data analyses and interpretation. Part of the interpretation concerns the integration of qualitative and quantitative outcomes.

The qualitative part of our study is used to elaborate on the preceding quantitative pilot outcomes and to discuss further interpretations of the quantitative quasi-experimental pre-post study outcomes. This qualitative part can help to gain insight into underlying mechanisms influencing parent participation and is therefore considered explanatory [31]. Understanding these mechanisms can contribute to overcoming possible obstacles in organizing family-oriented activities and can therefore improve FC.

The quantitative part in the second stage of our study will be carried out parallel to the qualitative part. This quantitative part is a pre-post comparison of two programs–FC and UC–for adolescents placed in short-term stay groups of two JJIs. This comparison is quasi-experimental, as no randomization will take place in assigning youth to either a FC or a UC group.

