### Setting

This study will be carried out in two JJIs in the Netherlands. A juvenile judge can refer an adolescent to a short-term stay group in a JJI for pre-trial detention. Depending on the interim ruling of the juvenile judge, the time spent in pre-trial detention can last for a few days up to a maximum of customarily 90 days. As a rule, the juvenile judge refers the adolescent to a JJI close to the home of the youth. The JJI’s secretarial office monitors a group’s capacity and decides on which group the adolescent is placed.

One of the JJIs has three short-term stay groups. The management of this institution chose two of these groups for a step-by-step implementation of the FC program, while the third group will continue to offer UC. Of the two short-term stay groups in the other JJI, the management chose one to offer FC, and the other UC. The managements of the two JJIs based their choices for the groups starting with the implementation of FC on pragmatic considerations. Because the JJIs are required to fill free slots in the living groups if new adolescents are referred to the institutions, the assignment of adolescents to groups is not dependent on characteristics of youths and is therefore without bias.

Each team of about 10 group workers is headed by a team leader and collaborates with a psychologist or pedagogue (hereafter jointly referred to as psychologist), who is responsible for coordinating the treatment the adolescent will receive.

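### FC and UC differ in JJI mix by design, yet JJI and other covariates enter the analysis only conditionally and the tests listed for hypotheses 1–7 take no covariates

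*Protocol article*

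**What the plan says.** The Design section is open about the lack of randomisation: "This comparison is quasi-experimental, as no randomization will take place in assigning youth to either a FC or a UC group". The Setting section describes how program and institution relate. In the institution with three short-term stay groups, the management "chose two of these groups for a step-by-step implementation of the FC program, while the third group will continue to offer UC". For the other institution: "Of the two short-term stay groups in the other JJI, the management chose one to offer FC, and the other UC". The managements "based their choices for the groups starting with the implementation of FC on pragmatic considerations". Which institution a boy enters depends mainly on where he lives, since as a rule "the juvenile judge refers the adolescent to a JJI close to the home of the youth". Within an institution, the secretarial office decides on the group. Because free places have to be filled, the article concludes that "the assignment of adolescents to groups is not dependent on characteristics of youths and is therefore without bias".

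On adjustment, the Quantitative Analyses section sets two conditional rules. For demographic factors: "We will test if these groups differ on demographic factors. If these differences exist, we will use these factors as covariates in our analyses". For institution: "If necessary, we will also include the JJI in which an adolescent is placed as a covariate". Nothing says when it would be necessary.

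Table 3 gives an unpaired t test or a Pearson chi-square test for each of hypotheses 1 to 7. Only the two staff-questionnaire rows (hypothesis 8) name models that can hold covariates: generalized estimating equations and a general linear model. A repeated measures ANOVA is named for combining pre-post and between-group comparisons. The final choice of test is left until the data are in.

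**The concern.** In a non-randomised comparison, adjustment is the main protection against confounding. Here one confounder is known before any data arrive: FC makes up two of three groups in one JJI and one of two in the other, and the JJIs serve different home areas. Any difference between the JJIs in population, regime or recording practice enters the crude FC–UC contrast. Leaving JJI to an undefined judgement, possibly made after seeing results, leaves that bias in or out at the analyst's discretion.

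The rule for the other covariates has a different fault. A balance test measures whether an imbalance is large relative to sampling error. It does not measure whether the factor distorts the effect estimate. At this sample size it often misses imbalances that matter.

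The promise of covariates also sits badly with Table 3. The mismatch is sharpest for parental visits, incidents and return home. These have no pre-measure, so the repeated measures ANOVA is not available as the route to adjustment.

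**Working it through.** **Inputs.** From the article: five groups of 10 places each (Introduction); FC:UC of 2:1 and 1:1 (Setting); 160 adolescents expected (Recruitment and Sample Size); two-tailed tests (Quantitative Analyses). Assumed: all groups fill equally, both FC groups in the first JJI deliver FC throughout, and alpha is 0.05, which the article does not state.

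**The plan's own figure.** The 160 cannot be reproduced, because no effect size, SD, alpha or power is given. For scale, a 96:64 split has standard error √(1/96 + 1/64) = 0.161 SD and detects (1.960 + 0.842) × 0.161 = 0.45 SD with 80% power.

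**Imbalance by JJI.** 160 / 5 = 32 boys per group.

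| | First JJI | Second JJI | Total | Share from first JJI |
|---|---|---|---|---|
| FC | 64 | 32 | 96 | 66.7% |
| UC | 32 | 32 | 64 | 50.0% |

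**Bias in the crude contrast.** If outcomes differ between JJIs by D (in SD units), bias = D × (2/3 − 1/2) = D/6. Type I error was simulated with 40,000 runs per value of D and no true FC effect.

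| Assumed D | Bias (SD) | Type I error, no JJI term |
|---|---|---|
| 0.3 | 0.050 | 0.058 |
| 0.5 | 0.083 | 0.071 |
| 0.8 | 0.133 | 0.105 |
| 1.0 | 0.167 | 0.124 |

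With JJI in a linear model, the bias is zero and simulated type I error lies between 0.049 and 0.052 for every D tried.

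For a binary outcome such as return home, take assumed rates of 70% and 50% in the two JJIs. The FC rate is 0.70 × 2/3 + 0.50 × 1/3 = 63.3% and the UC rate is (0.70 + 0.50)/2 = 60.0%. That is a spurious difference of 3.3 points.

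**Cost of always including JJI.** The share of boys both in FC and in the first JJI is 64/160 = 0.40. The covariance of program and JJI is 0.40 − 0.60 × 0.60 = 0.04, and each variance is 0.60 × 0.40 = 0.24, so the correlation is 1/6. The standard error is multiplied by 1/√(1 − 1/36) = 1.014.

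**The significance gate.** For a true imbalance of 0.3 SD at 96 versus 64, 0.3/0.161 = 1.86, and the probability of exceeding 1.96 is about 0.46. For 0.2 SD it is about 0.24. If a 0.3 SD imbalance in a factor correlated 0.5 with outcome (assumed) were never adjusted for, the bias would be 0.3 × 0.5 = 0.15 SD and type I error about 0.15. The gate does better than that, because it catches the samples with the largest observed imbalance. It still leaves the true imbalance uncorrected in about half of them.

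**The case against.** The strongest defence is that the article does provide for adjustment. It names JJI as a possible covariate, promises to use demographic factors that differ, and leaves the final tests open. Table 3 can be read as the basic test per hypothesis, with a covariate-capable model to follow when needed. This stands in part. A reader might infer that adjustment cannot happen for hypotheses 1–7, but the text does not support that. The adjusted model is unnamed, not excluded, and the staff rows already use models that accept covariates.

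A reader might also infer that housing, past treatment and schooling are ignored. They are not: the article collects them under its Demographics heading, so they belong to the factors to be screened. The gate is the fault, not the candidate list.

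A third tempting step is to show from the expected intake and number of places that beds were often free, and so that placement was selective. The article gives no distribution of stay lengths, and 90 days is only the customary maximum for pre-trial detention. Its exclusion criteria show that returning, sentenced and transferred boys may also occupy places. A duty to fill free places already presupposes vacancies, and having a choice of group is not evidence of choosing by a boy's characteristics. Placement within a JJI may well be close to haphazard.

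Two points on size also stand. The bias from JJI alone is modest: 0.083 SD at D = 0.5 is under a fifth of the 0.45 SD the study can detect. And the gate always flags an observed imbalance above about 0.32 SD (roughly 1.975 × 0.161).

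None of this justifies making JJI optional. Slot-filling within an institution cannot remove an imbalance created between institutions, nor selection after placement through short stays, refusal or psychologists withholding families (Participants section).

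**Conclusion.** The point holds as a should-fix. The association between program and JJI is built into the design, and the stated rules make correction for it optional. They also make correction for other factors depend on a weak test. One sixth of any JJI difference passes into the unadjusted FC effect. This fraction rests on equal filling and on a constant 2:1 ratio in the first JJI, and it would change if the second FC group there started later or groups filled unevenly. The 0.083 SD and type I error of 0.071 rest further on an assumed JJI difference of 0.5 SD. The documents give none, so the actual bias could be negligible or larger. The 46% rests on the 96:64 split and alpha of 0.05.

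The article's statement that assignment is free of bias goes beyond what its placement mechanism can support. That is a claim to qualify; the documents do not show that boys were selected into FC.

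**What to change.** 1. Include JJI in every FC–UC model for hypotheses 1–7, without condition.
2. Adjust for a list fixed in advance from the demographics already collected: age, ethnic background, housing, past treatment, and school or work. Keep the list whatever the balance tests show. Questionnaire baselines are less suitable for it, because they are taken in the third week of detention, after FC has begun.
3. For hypotheses 1–7, replace the t and chi-square tests with linear, logistic or count regression according to the outcome, so that the promised adjustment has a named method. This matters most for visits, incidents and return home.
4. Replace the claim of unbiased assignment with a statement that filling free places may limit selection within a JJI, but does not remove confounding by JJI or selection after placement.

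The cost is a change of analysis wording, a few degrees of freedom, and about 1.4% in standard error for the JJI term. No new data are needed.

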We decided to examine if FC is beneficial for detained youths and their parents. We report here on the design of a study to evaluate FC in the first two years after the first steps of its implementation in short-term stay groups. Each short-term stay group has room for 10 adolescents. The groups are supported and monitored by JJI staff, so-called group workers (mostly social workers). The aim of the current paper is to describe the study protocol and to stress the potential of research studies in a challenging setting such as a JJI with its ethical dilemmas, the unfamiliarity of staff with research methodology, and with a difficult population with low treatment motivation [22-24].

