### Recruitment and Sample Size

Adolescents and parents are informed of the JJI’s research activities by a flyer in the information leaflets from the JJI. The flyer informs that the data will be used anonymously in research studies and that parents can address their questions concerning these activities to their child’s mentor (one of the group workers) or to the psychologist.

The JJIs in the Netherlands jointly apply ROM and standard screening and diagnostic procedures for detained adolescents and their parents. As our assessments will be embedded in these procedures, the quantitative part of our study will use data collected in the two participating JJIs by these means. Recruitment of adolescents and their parents in the quantitative part of our study will last 21 months, including the pilot stage of 7 months. Based on records from 2011, the year prior to the pilot stage, we estimate that in 21 months, 300 adolescents will be placed in the groups concerned. Taking into account the exclusion criteria, we expect to recruit 160 adolescents and parents for the present study. Based on previous research, this number suffices for establishing statistically significant differences on quantitative measures between the two conditions [9].

As for qualitative studies, 10 interviews are generally sufficient to achieve saturation (ie, the point where additional interviews do not yield new essential information regarding the research question) [32]. Once an eligible adolescent is placed in a short-term stay group (either FC or UC), he and his parents will be invited to participate in the qualitative part of the study. If they are willing to participate, an appointment will be made for the interview. We will interview 10 boys (5 aged < 16 years and 5 aged > 16 years) in each JJI (N=20). We will also interview 20 parents (10 in in each JJI, 10 fathers and 10 mothers, 10 with a detained child aged < 16 years, and 10 with a detained child aged > 16 years). Finally, we will interview 20 FC group workers and 20 UC group workers.

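### FC or UC is assigned to five whole living groups, but Table 3 tests youth and parent outcomes as if boys were independent, so p-values are too small for any outcome with a living-group correlation

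*Protocol article*

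**What the plan says.** **Assignment (Setting).** In the first institution, management "chose two of these groups for a step-by-step implementation of the FC program, while the third group will continue to offer UC". For the second: "Of the two short-term stay groups in the other JJI, the management chose one to offer FC, and the other UC". That makes five living groups, three FC and two UC. Each has its own team of about 10 group workers, with a team leader and a psychologist. The Design section confirms that "no randomization will take place in assigning youth to either a FC or a UC group".

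**Analysis (Quantitative Analyses, Table 3).** The comparison factor is FC or UC. "Table 3 shows the planned analyses to test our hypotheses for comparing FC with UC in case of normally distributed data". For hypotheses 1 to 7 the table lists unpaired t tests and Pearson chi-square tests. Generalized estimating equations and general linear model repeated measures appear only for the staff questionnaires (hypothesis 8). The text adds demographic covariates if the conditions differ on them, institution as a covariate if necessary, repeated measures ANOVA, and a correction for multiple testing.

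**Sample size (Recruitment and Sample Size).** "we expect to recruit 160 adolescents and parents for the present study", and the article says "this number suffices for establishing statistically significant differences on quantitative measures between the two conditions". It gives no effect size, standard deviation, power, ICC or design effect.

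**The concern.** The unit that receives FC or UC is the living group with its team, and there are only five. FC works through trained staff and their contact with parents, so the team is part of the treatment. Boys in one group are visited under the same team's practice, live and quarrel together, and rate the same staff. The Design section reports that FC groups differed in their family-oriented actions during the pilot although all workers had the same training. That is variation between teams within one condition.

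An unpaired t test or Pearson chi-square test counts every boy as independent evidence. If boys in a group are positively correlated, the standard error is too small, and an ordinary difference between three teams and two teams can be reported as an effect of FC. These tests answer the article's key question, whether FC adds value over UC.

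This is not a detail left to an unseen analysis plan, because the article names the tests.

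**Working it through.** **1. The plan's own figure.** The 160 cannot be reproduced, because no effect size, power or significance level is stated. Working backwards, assume two-sided alpha 0.05, 80% power and an even spread over five groups: 160/5 = 32 per group, so 96 FC and 64 UC. Under independence the detectable standardised difference is

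(1.96 + 0.842) × √(1/96 + 1/64) = 0.45,

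and nominal power for d = 0.5 is 0.87.

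**2. Does anything in the plan handle living group?**
- Institution as covariate: optional, and one level above living group.
- Demographic covariates: address imbalance between conditions, not dependence within groups.
- Repeated measures ANOVA: handles repeats within a person.
- Multiplicity correction: operates on p-values that are already too small.
- Non-normal alternatives: the choice of test is tied to hypothesis and data type, not to clustering.

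**3. Effect on the t test.** Inputs: five groups (Setting); 160 boys (Recruitment and Sample Size); even spread, alpha 0.05 and ICC 0.01 to 0.10 (all assumed). Formulas:
- design effect DE = 1 + (m − 1) × ICC
- effective n = 160/DE
- true type I error = 2 × [1 − Φ(1.96/√DE)]

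Example, m = 32 and ICC 0.05: DE = 1 + 31 × 0.05 = 2.55; effective n = 160/2.55 = 63; standard error ratio √2.55 = 1.60; type I error = 2 × [1 − Φ(1.227)] = 0.22.

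| ICC | DE (m = 32) | Effective n | Type I, formula | Type I, simulated | Type I, m = 20 |
|---|---|---|---|---|---|
| 0.01 | 1.31 | 122 | 8.7% | 8.7% | 7% |
| 0.02 | 1.62 | 99 | 12.4% | 12.4% | 10% |
| 0.05 | 2.55 | 63 | 22.0% | 22.5% | 16% |
| 0.10 | 4.10 | 39 | 33.3% | 34.2% | 25% |

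The simulation used 40,000 null trials per ICC, with three against two groups of 32. At ICC 0 the t test rejected in 5.1%. The last column assumes 20 analysable boys per group (DE 1.19, 1.38, 1.95, 2.90). For Pearson chi-square on a median-split outcome with the same underlying ICCs and 32 per group, the simulated error was 7.5%, 9.6%, 16.7% and 26.2%.

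**4. Group-level comparison.** A t test on the five group means (3 df) held its error at 4.9% to 5.2% throughout. Its power comes from the noncentral t distribution with noncentrality 0.5/√[(DE/32) × k]. Here k = 1/3 + 1/2 = 0.833 on 3 df. With institution as a fixed effect, k = 1/(2/3 + 1/2) = 0.857 on 2 df.

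| ICC | Power, 3 df | Power, 2 df |
|---|---|---|
| 0.01 | 0.46 | 0.33 |
| 0.02 | 0.39 | 0.28 |
| 0.05 | 0.28 | 0.21 |
| 0.10 | 0.19 | 0.15 |

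**5. Mixed model.** With five groups of 32, the between-group variance is estimated as zero whenever the between-group mean square falls below the within-group one. This happens in about 48% of trials at ICC 0.01 and 39% at 0.02. The model then reduces to the pooled analysis unless its degrees of freedom are fixed.

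**The case against.** **Inflation depends on the outcome.** A reader might infer that all seven youth and parent hypotheses are affected alike. The documents do not support that. Inflation needs an ICC above zero and none is given. Family interactions, parenting stress and return home are largely family attributes, and the Setting section says boys fill free places regardless of their characteristics. The pilot evidence concerns staff actions, not youth or parent outcomes. This stands, and the conclusion is conditional on the ICC.

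**The figures may be high.** The calculation treats all 32 boys in a group as equally correlated. Yet "Each short-term stay group has room for 10 adolescents", stays are customarily at most 90 days, recruitment runs 21 months and staff turnover is high, so many boys never overlap. Including institution would also remove any between-institution part of the correlation. This stands as a reason to read the results as a range, hence the column for 20 per group. Even there, ICC 0.01 gives 7%.

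**Table 3 is provisional.** It covers normally distributed data, and final tests are chosen after data collection. True, but none of the stated alternatives brings in living group.

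**Two parents of one boy.** A reader might infer that two parents' answers are treated as independent. The article does not say that both complete the questionnaires, or how two responses would be handled. The equal numbers of fathers and mothers it mentions belong to the interviews. No point is made of it.

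**Conclusion.** The point holds in conditional form. For hypotheses 1 to 7 the named tests do not match the unit of assignment, and no other element of the plan corrects this. Any outcome with a positive living-group ICC will have p-values that are too small. Visits, motivation, incidents and satisfaction are the likeliest, since team and peer group shape them.

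The size rests on assumed values: alpha 0.05, an even spread over five groups, and ICC 0.01 to 0.10. On those, a nominal 5% t test has a true error of about 9% to 33-34% with 32 boys per group, or 7% to 25% with 20. The staff rows of Table 3 lie outside the point.

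The statement that 160 is enough cannot be relied on for this design. With two or three groups per condition, the effect of FC cannot be well separated from that of the teams, so the results support exploratory rather than confirmatory claims.

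**What to change.** - For youth and parent outcomes, replace the Table 3 tests by an FC-UC comparison at living-group level: adjusted group means on 3 df, or 2 df with institution as a fixed effect.
- If a mixed model with a random living-group intercept is preferred, fix its denominator degrees of freedom at the group level. With five groups it is not otherwise interchangeable with the group-means analysis, because of the zero variance estimates shown above.
- Show the individual-level tests as descriptive only, with sensitivity results at ICC 0.01 to 0.10.
- Limit the conclusion to these five groups, and withdraw or qualify the sample-size statement.

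**Cost.** The programming is minor, but the loss of power is not. For d = 0.5, a nominal 0.87 falls to about 0.46-0.19 on 3 df or 0.33-0.15 on 2 df, before the multiplicity correction. The Discussion says data collection is complete, so groups cannot be added. Only the analysis and the strength of the claims can still change.
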